## 7. Recruitment

The study will be advertised to people aged 16-years and over with ID and their carers via the Institute’s social media channels and through promotional activities by our existing partner networks (e.g., ID researchers, clinicians, and advocacy groups). The recruitment message for the study focusses on learning new ways to manage difficult thoughts and feelings. Each study participant will also nominate a trusted carer (or carers) to provide support throughout all trial stages. Consent, screening, and all other data collection will be completed online with carer support. Diagnosis of ID will be confirmed by the nominated carer, and an estimate of cognitive functioning will be obtained using the CBS Health online cognitive assessment tool.

## 8. Assignment of Interventions

### 8.1. Allocation

Participants are allocated to a condition following a 1:1 allocation ratio using computerised blocked randomisation with blocks of eight. Randomisation occurs immediately after a participant completes the baseline assessment, ensuring allocation concealment.

### 8.2. Blinding

Participants will remain blind to study allocation during the intervention and follow-up periods; however, study helpers in the waitlist condition will be unblinded.

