## 3. Trial Design

The study described here is a two-arm individually randomised controlled trial (RCT) conducted wholly online. Participants allocated to the intervention group will have full access to the Healthy Mind program for 8 weeks. Participants randomised to the control group will be placed on a waitlist for 8 weeks and given full access to the Healthy Mind program after their waitlist period expires. Participants in both groups will have uninterrupted access to treatment as usual for the duration of their study participation.

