#### 4.1.2. Eligibility Criteria

Participants will be eligible to participate if they are aged 16 years or over, have documented ID in the borderline or mild range, report mild-to-moderate symptoms of depression and/or anxiety, and are computer and internet literate. In addition, each study participant will be required to nominate a trusted carer to provide support throughout all trial stages. Consent, screening, and all other data collection will be completed online with carer support.

Participants will be ineligible if they have an ID diagnosis in the moderate range or above, report severe mental health problems (severe symptoms of anxiety and/or depression, severe mood disturbance and/or mania, suicidal ideation, psychotic symptoms), or are experiencing medical comorbidities or other functional impairments that might impede trial engagement (e.g., impaired vision, hearing, motor skills, etc.). Ineligible participants will be offered the opportunity to participate in the community collaboration aspect of our dissemination plan, which will involve giving lived-experience feedback on the trial results and recommendations about how future trials and services for people with ID should be designed. Any potential participant reporting severe mental health symptoms will be referred to their general practitioner for further assessment. Participants reporting acute distress will be referred to phone services offering immediate support including, Lifeline, Kids Helpline, and the Suicide Call Back Service.

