#### 4.1.3. Interventions

Active intervention (Healthy Mind): Healthy Mind (www.healthymind.org.au) is a first-of-kind, fully automated, web-based eMH program tailored to the needs of people with ID (Figure 1). Participants randomised to the active intervention condition have access to the full Healthy Mind program for 8 weeks. Healthy Mind comprises five interactive activities (Figure 2) designed collaboratively by ID consumers and experts: (1) the “Recognising feelings” activity helps users to identify and regulate negative emotions (e.g., sad, angry, and worried); (2) “Breathe and relax” helps users understand how to use controlled breathing to calm strong emotions and be more present in their everyday life; (3) “Taming anger” offers users strategies for reducing frustration and improving communication when feeling overwhelmed; (4) “Having more fun” suggests enjoyable activities involving socialising, exercise, and leisure. The activity helps users to integrate fun activities into their regular routines, using a weekly planner; and (5) the “Tackling unhelpful thinking” activity translates core aspects of cognitive therapy into simple strategies for re-appraising stressful thoughts.

Each activity is presented in easy-read English and has two sessions that follow a three-step process (Figure 3): (1) “Learn about it”; (2) “Watch it”; and (3) “Do it” [36]. At step 1, users read an introduction to the topic and explanation of its impacts and value. At step 2, users watch a brief video tutorial demonstrating what the skill or behaviour looks like, enacted. At step 3, users are presented with opportunities to practise the new skill or behaviour with guided visual or audio instructions, interactive activities, and using a worksheet available for download. The program design was developed based on user feedback, elicited during the feasibility and accessibility trial [37]. For example, users requested a highly simplified structure involving early access to the videos, which were to be presented separately to the participatory components. To further enhance accessibility, users can click an icon to hear the words on the screen read aloud throughout each activity, and an animated dog is always at hand to provide support using a chat interface. Healthy Mind also offers educational and support resources for carers and emergency contact options for users who may be experiencing significant distress.

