Pilot testing of Healthy Mind revealed that a sufficiently robust password system was a barrier to access due to the different language and memory abilities of users, given the site is intended for independent use by some consumers in the future [37]. Therefore, the Healthy Mind site does not require a login. User privacy is maintained by ensuring each user session is secure and unidentifiable. This is achieved by removing all opportunities to enter identifiable information (e.g., users are never asked to provide their name or any other identifiers). Identifiable information is only entered into a separate study website (detailed below).

The absence of a login system in the intervention poses a challenge for monitoring engagement with the treatment. Although this is not ideal methodologically, our priority has been to create an accessible website. This priority was identified in our co-design process previously described in our team’s publication [37]. Treatment engagement will therefore be assessed retrospectively by self-report at the first follow-up measurement.

Waitlist control group: The control group will be advised that there will be a delay in being able to access to Healthy Mind and that they will receive an email from the research team as soon as the website is available to access (i.e., after the three-month follow-up survey has closed). Control group fidelity will be maintained by collaborating with study helpers to avoid access to Health Mind and surveying control participants after the 8-week period to ensure that they were not exposed to Healthy Mind.

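### Section 8.2 says participants stay blind to allocation, but an access-versus-waitlist design cannot blind them to whether they have the program

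*Protocol article*

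**What the plan says.** Section 8.2 (Blinding) consists of one sentence with two claims, the first on participants and the second on helpers: "Participants will remain blind to study allocation during the intervention and follow-up periods; however, study helpers in the waitlist condition will be unblinded". It does not mention helpers in the intervention arm.

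Section 3 (Trial Design) sets out what each arm receives. For the active arm: "Participants allocated to the intervention group will have full access to the Healthy Mind program for 8 weeks". For the comparator: "Participants randomised to the control group will be placed on a waitlist for 8 weeks". Usual care continues in both arms, and no sham or attention-matched program is described.

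Section 4.1.3 (Interventions) repeats the active condition: "Participants randomised to the active intervention condition have access to the full Healthy Mind program for 8 weeks". Of the waitlist it says: "The control group will be advised that there will be a delay in being able to access to Healthy Mind". It adds that an email will follow when the site can be used, that helpers will be enlisted to keep controls off the site, and that controls will be surveyed after week 8 to check that they had not been exposed.

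On how outcomes are obtained, Section 4.1.2 (Eligibility Criteria) says: "Consent, screening, and all other data collection will be completed online with carer support". Section 7 repeats this. Section 4.1.4 describes the ADAMS and the WHO-DAS as self-report, and Section 9.1 says that the self-report questionnaires are completed online.

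**The concern.** Section 8.2 claims for the trial a safeguard that its procedures do not provide. A participant who is working through Healthy Mind knows it, and a participant who has been told to wait for it knows that too.

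This matters because all three efficacy measures are questionnaires completed by the participant with a carer's support. With such outcomes, knowing whether one has received the program can affect the answers through expectation, or through disappointment at waiting. Participant blinding is the feature that would guard against this. A reader who takes Section 8.2 at face value would credit the trial with that protection when interpreting an ADAMS difference. Section 12 (Limitations) discusses volunteer bias and attrition but not this, so nothing elsewhere corrects the impression.

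Lack of blinding is usual in a waitlist trial of a web program and is not itself the criticism. The criticism is of a positive statement that the protocol contradicts.

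**Working it through.** No figure in the protocol bears on this point, so the check sets the passages side by side.

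1. **What Section 8.2 would require.** For participants to be blind to allocation throughout intervention and follow-up, nothing they see or are told may reveal which arm they are in.

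2. **Intervention arm.** Sections 3 and 4.1.3 give these participants full use of a named, visible website for 8 weeks. There is no alternative program that they could mistake it for. They know that they have it.

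3. **Waitlist arm during the 8 weeks.** Section 4.1.3 has controls told that access to Healthy Mind, by name, is delayed. They know that they do not have it.

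4. **Waitlist arm after week 8.** Section 4.1.3 has controls asked about exposure to Healthy Mind. The article does not date this survey more closely than after the 8-week period. A question of this kind again draws attention to not having had the program. The sections differ on whether access opens after the 8-week wait (Section 3) or once the three-month survey has closed (Section 4.1.3). On either reading controls know their own access status, so the result does not depend on which applies.

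5. **Comparator.** With no sham or attention control, having the program and being in the active arm amount to the same thing. Receipt of the program cannot be masked.

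6. **Helpers.** Section 8.2 itself says that waitlist helpers are unblinded, and Section 4.1.3 asks them to keep controls off the site. For intervention-arm helpers Section 8.2 is silent. However, Sections 4.1.2 and 7 have carers supporting participants at every trial stage, so such a helper would see that the program is in use.

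7. **Link to the outcome.** Sections 4.1.2 and 7 attach carer support to data collection generally, and Section 5 uses the word helper for the person who supports the baseline questionnaires. The one task described as done alone is the CBS Health cognitive assessment, which Table 1 places at baseline only. The ADAMS, K10 and WHO-DAS at 8 weeks and at follow-up therefore fall under the general statement of carer support.

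Result: steps 2 to 5 contradict the first half of Section 8.2. Steps 6 and 7 do not contradict the second half. They show why the contradiction bears on the primary outcome.

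**The case against.** The best defence is that Section 8.2 means something narrower. Controls are told only of a delay and promised an email when the site opens. They might take this for a late launch while their helpers know that it is a control arm. The consent and information text that would settle this is not shown. This stands as a possibility, and the fix allows for it. But it would mask only the label, not receipt of the program, and receipt is what drives expectation. Section 8.2 does not limit its claim in this way. The reading also does nothing for the intervention arm.

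Four stronger readings are tempting, and the documents do not support them:

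- A reader might infer that the protocol claims intervention-arm helpers are blind. It does not; it says nothing about them. The unblinding of waitlist helpers is openly disclosed.
- A reader might infer that helpers answer for participants. Support is not proxy completion, the questionnaires are described as self-report, and the abstract speaks of carer help where necessary.
- A reader might infer assessor bias. The questionnaires are sent automatically and completed online, so no interviewer is involved.
- A reader might infer that helper influence favours the program. Nothing in the documents fixes its direction.

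It can also be said that the article plainly describes a waitlist trial, so few readers would be misled. That lessens the harm, but it does not reconcile Section 8.2 with Sections 3 and 4.1.3.

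**Conclusion.** The point holds as an inconsistency that should be corrected. The unqualified statement of participant blinding in Section 8.2 cannot be reconciled with Sections 3 and 4.1.3. Participants in both arms know whether they have the program; at most the control label is hidden. Because the ADAMS is self-reported with carer support, and waitlist carers know the allocation, a difference against waitlist cannot be taken as free of expectancy and reporting effects.

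The size of any such effect cannot be computed from the documents. A reader might set an assumed reporting shift of 0.1 to 0.2 SD against the planned 0.5 SD in Section 6 and call it 20 to 40% of the effect (0.1/0.5 and 0.2/0.5). That is only the guess divided by 0.5, and it carries no weight here. The conclusion rests on the text alone. It assumes that the waitlist notice is given as Section 4.1.3 describes and that there is no undisclosed sham. Sample size, randomisation, outcomes and the primary analysis are unaffected.

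**What to change.** **Section 8.2.** Replace the sentence with a statement that participants and helpers in both arms are not blinded to receipt of the program, and that outcomes are participant-reported with helper support. If controls are in fact not told that they are a control group, say so, and say that only this label is masked.

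**Section 12 (Limitations).** Add that the ADAMS, K10 and WHO-DAS contrasts against waitlist may include expectancy and reporting effects.

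**Efficacy conclusion.** Word it as an effect of access to the program compared with waitlist, which may include those effects. The hypotheses in Section 2 are already framed relative to the control group, so the explicit mention of expectancy is the only addition.

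**Not recommended.** Do not add a sensitivity analysis that splits the ADAMS contrast by whether the survey was completed alone or with help. That is recorded after randomisation, may itself differ between arms, and can introduce bias. It also leaves participants' own knowledge of their access untouched. If completion mode is recorded at all, report it descriptively. Section 9.1 describes data collection as under way, so earlier participants could lack the item, and adding it may need an ethics amendment.

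**Cost.** Wording only. The downside is a less favourable risk-of-bias statement.

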## 9. Data Collection, Management, and Analysis

### 9.1. Data Collection

All self-report data are being collected electronically via standardised, self-report questionnaires that are completed via the Healthy Mind study website (described above). At each assessment point, the study website automatically issues a unique link to the study questionnaire via email. Questionnaire data are kept on a secure server at University of New South Wales (UNSW), Australia, and downloaded periodically for storage in a password-protected data file accessible by [name] and [name]

Cognitive function data are being collected electronically using CBS Health assessments administered via the CBS website (described above). All data will be encrypted during transmission to and storage on Amazon’s AWS EC2 service (OR, USA). Once stored, it will be accessible by only [name] and [name] on the password-protected platform. The only other individuals with access to the trial data are the CBS administrators, who may access the researcher account in case of a technical issue or emergency.

### 9.2. Retention

To maximise study engagement and retention, participants who complete questionnaires at each measurement point will receive a shopping voucher worth $20 Australian Dollars (AUD) for both themselves and their nominated carer. A scheduled reminder system is also being used to further motivate questionnaire completion. Participants and carers who do not respond to the scheduled prompt sent by email and short message service (SMS) will receive a phone call reminder from a trial team member.

### 9.3. Statistical Analysis

Statistical analyses will be performed using SPSS 25.0 (IBM Inc., Armonk, NY, USA) and MPlus (Muthen & Muthen, Los Angeles, CA, USA). Intention-to-treat analyses will be used to establish change across time and any treatment effects using linear mixed models for repeated measures (MMRM). Missing data will be handled using maximum-likelihood estimation within the MMRM procedure, as this appears to be more robust to violations of the assumption of randomness due to attrition [45]. Where appropriate, complier analyses will be used to estimate the effect of treatment-as-recommended using a complier average causal effect (CACE) procedure [46]. Cognitive sub-domain (e.g., speed of information processing) indices will be used as covariates in all analyses to determine whether cognitive profile impacts the use or efficacy of Healthy Mind. All effect sizes will be computed and reported using Cohen’s *d*.

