## 2. Objectives and Hypotheses

The primary aim of this study is to answer the research question regarding whether using a tailored eMH program (Healthy Mind) can reduce symptoms of anxiety and depression and improve daily functioning in people aged 16-years and over with borderline-to-mild ID. A secondary aim is to examine any effects that specific impairments in intellectual functioning (e.g., poor working memory) may have on engagement with, and benefits of, an eMH program. We predict that people who use the intervention will report reduced depression and anxiety, relative to the control group. We also predict that lower scores on tests of cognitive function will be related to lower engagement and benefit in the treatment group.

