The CBS Health assessment system will provide an estimate of four key areas of cognitive function: (1) The Digit Span task will provide an estimate of verbal working memory; (2) the Grammatical Reasoning task will provide an estimate of the ability to use verbal information to draw conclusions; (3) the Spatial Planning task will provide a measure of the ability to use visual information to plan ahead; and (4) the Feature Match task will test the ability to focus one’s attention on specific features of an image. (https://www.cambridgebrainsciences.com/).

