## 5. Participant Timeline

Participant consent, screening, and assessment will take place online via a secure study-specific website hosted on the Black Dog Institute research platform (https://healthymind.blackdoghealth.org.au), which is separate from the intervention site. The research platform is password-protected; therefore, participants may require support from their helper during this component of the study. Once on the secure site, potential participants and their helper will complete the online screening questionnaire to establish eligibility. Eligible participants and their helper will then each provide informed consent online by reviewing and agreeing to the participation information and consent statement. After providing informed consent, eligible participants will be directed to a secure website where they will enter contact details and complete the baseline questionnaires with support from their helper, then complete the CBS Health cognitive assessment independently. To allow for participant fatigue, all online assessments can be paused and resumed at a later date. Ineligible participants will receive automated feedback explaining that the study is not right for them, based on their answers. Details of telephone counselling support (e.g., Lifeline) and other self-help and face-to-face resources will be provided as appropriate.

After baseline assessment, eligible participants will be randomly allocated to one of two conditions using computerised block randomisation at a 1:1 allocation ratio: (1) the intervention condition, in which participants have full access to the Healthy Mind program; or (2) the control condition, in which participants are placed on a waitlist and given access to Healthy Mind at the conclusion of the waitlist period. Subsequent assessment points coincide for both groups at post-intervention (8 weeks) and 3 months after randomisation. The full flow of participants is presented in Figure 4.

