## 6. Sample Size

The primary outcomes for this study are depression and anxiety symptoms (measured using the ADAMS). Meta-analysis of psychological therapies for people with ID suggests an expected effect of treatment on similar measures of anxiety and depression symptoms of approximately 0.6 [43]. However, this is based on face-to-face treatments and may represent an overestimation [44]. To detect a more conservative effect size of ~0.5, we will need a minimum of 50 participants per group, therefore we will recruit a sample of approximately 167 individuals to allow for ~40% attrition. This calculation was based on the group differences on ADAMS between waitlist control and intervention groups at 8 weeks and 3 months, assuming 80% power and alpha = 0.05 (0.025 for each primary group difference), in order to detect a mean difference of 0.5 standard deviation units at 8 weeks and at 3 months.

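### Cognition enters the analysis only as a covariate, which does not test whether it changes the benefit of Healthy Mind; the benefit half of the secondary aim needs an arm-by-cognition term

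*Protocol article*

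**What the plan says.** Section 2 of the protocol article sets a secondary aim: to examine effects that specific cognitive impairments "may have on engagement with, and benefits of, an eMH program". The attached prediction is that "lower scores on tests of cognitive function will be related to lower engagement and benefit in the treatment group".

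The only analysis given for this aim is in Section 9.3. After describing an intention-to-treat MMRM, it says that cognitive sub-domain indices "will be used as covariates in all analyses to determine whether cognitive profile impacts the use or efficacy of Healthy Mind". No arm-by-cognition term, moderation analysis or comparison of arms by level of cognition is named anywhere in the article.

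On measurement, Section 4.1.4 says: "The CBS Health assessment system will provide an estimate of four key areas of cognitive function". The areas listed are verbal working memory, verbal reasoning, spatial planning and attention to visual features. The example index in Section 9.3 is processing speed, which is not among them. Section 5 says that participants "complete the baseline questionnaires with support from their helper, then complete the CBS Health cognitive assessment independently", and Section 8.1 places randomisation after the baseline assessment. Section 4.1.3 says that engagement will be measured by retrospective self-report at the first follow-up.

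**The concern.** Efficacy in a randomised trial is a contrast between arms. To ask whether cognition affects efficacy is to ask whether that contrast changes with cognition, and the parameter for this is the arm-by-cognition interaction. Section 9.3 gives the question to a covariate coefficient, which is a different parameter. The text is therefore not merely silent on model detail: it names a method and assigns it a question that the method cannot answer.

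Two errors become possible. If people with lower cognition do worse in both arms alike, the covariate will often be significant and may be reported as an effect of cognition on efficacy when there is none. If cognition does change the benefit but its slopes in the two arms partly cancel, the covariate can miss it. At stake is a statement about who benefits from a program built for people with cognitive impairment.

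**Working it through.** **Inputs from the article.** 50 analysable participants per group and about 167 recruited (Section 6); 1:1 allocation (Section 8.1); four cognitive areas (Section 4.1.4); cognition measured before randomisation in both arms (Sections 5 and 8.1).

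**Assumptions not in the article.** One time point, no baseline ADAMS in the model unless stated, residual SD 1, cognition standardised to SD 1, two-sided 5% tests, and a range of slopes.

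**The plan's own figures.** The article gives no figure for the cognition aim. The recruitment figure reproduces: 100 / (1 - 0.40) = 167. The 50 per group for a 0.5 SD difference matches a one-sided 0.05 test; a two-sided 0.025 test gives 77. Nothing below depends on this; I take 50 per group as stated.

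**What each term estimates.** Write the outcome as y = a + b·arm + g·cog + d·(arm × cog) + error, where d is the moderation.
- Covariate coefficient when the product term is omitted, at 1:1: g + d/2, the average of the two arms' slopes.
- Treatment-arm-only slope: g + d.
- Interaction: d.

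Only the third is free of g, the prognostic slope. With g = 0 and d = 0.40 the covariate coefficient is 0.20. With g = 0.3 and d = -0.6 it is 0.3 - 0.3 = 0, although the moderation is large.

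**Standard errors.** Covariate: 1/√100 = 0.10. Treatment-arm-only slope: 1/√50 = 0.14. Interaction: √(1/50 + 1/50) = 0.20.

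**Simulation (4,000 trials per row, 50 per arm): share significant at 5%.**

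| Truth | Covariate | Treatment arm only | Interaction |
|---|---|---|---|
| No moderation, slope 0.2 | 49% | 29% | 5% |
| No moderation, slope 0.3 | 82% | 52% | 5% |
| No moderation, slope 0.4 | 97% | 77% | 5% |
| Moderation -0.6, slopes +0.3 (control) and -0.3 (intervention) | 6% | 53% | 81% |

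In the first three rows the interaction keeps its nominal error rate while the covariate responds to prognosis alone. In the last row the covariate is close to its 5% level although the moderation is large.

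**Dependence on baseline.** The treatment-arm-only column ignores baseline ADAMS. Suppose cognition relates equally to ADAMS before and after treatment (slope 0.4, residual correlation 0.5 to 0.7). The within-arm association is then significant in about 19% to 29% of trials with baseline as a covariate, and in about 5% for change scores.

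**Precision of the correct test.** Power ≈ Φ(d/0.20 - 1.96): 17% for d = 0.2, 32% for 0.3 and 71% for 0.5. For 80% power, d = (1.96 + 0.84) × 0.20 = 0.56 SD per SD of cognition. Four such tests at 0.05 each, if independent, give a chance of at least one false positive of 1 - 0.95^4 = 18.5%.

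**The case against.** The strongest defence is that this is a condensed article. Section 9.3 states a moderation purpose, the word covariates can loosely include their interactions, and exact model terms are often left to a fuller plan. This stands in part: an interaction may yet be fitted. But the sentence does name a method for the purpose, and the prediction in Section 2 is worded for one arm, which points away from a two-arm test. One added sentence would remove the doubt.

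A reader might infer that the benefit prediction will be tested by a correlation in the intervention arm alone, and quote 77% as the chance of false support. The article does not support that. Section 9.3 puts cognition into all analyses, which are intention-to-treat and so cover both arms. The wording in Section 2 is a hypothesis and may mean only that benefit arises where the program is given. The 77% also needs a slope of 0.4 and no use of baseline: about 10% at a slope of 0.1 and 29% at 0.2, less with baseline adjustment, and near 5% for change scores in the case shown.

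A reader might also infer that the secondary aim cannot be answered at all. That goes too far. Only the intervention arm has the program during the first eight weeks, so a within-arm analysis is the right one for engagement.

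Last, the interaction has low power. That is true and must be reported, but it does not make the covariate coefficient an answer to the question.

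**Conclusion.** The point holds for the benefit half of the secondary aim. As written, the covariate coefficient estimates the average of the arms' slopes and not their difference, so it can be significant with no moderation (about 49% to 97% for slopes of 0.2 to 0.4) and can miss a large moderation (about 6% against 81% for the interaction when the slopes are opposite). That the covariate estimates a different quantity is algebra. The percentages rest on the assumptions listed and would change with other slopes, baseline adjustment or repeated measures.

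The engagement half is not affected. Nor is the primary efficacy estimate: adjusting it for covariates measured before randomisation is acceptable. The processing-speed example is a real but minor mismatch with the four areas listed, and it adds nothing to the moderation argument.

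**What to change.** - **Section 9.3, benefit.** State that moderation of benefit is assessed by adding arm x time x cognition, with all lower-order terms, to the MMRM in both arms for the measured CBS scores. Report each interaction with a 95% confidence interval and label the analysis exploratory. A multiplicity adjustment over the four scores is optional for an exploratory analysis.
- **Primary model.** Keep arm x time in the primary ADAMS model, because the 8-week and 3-month contrasts need it. Exclude only the cognition interactions. Cognition may stay as a covariate there, described as adjustment and not as a test of who benefits.
- **Section 2.** Reword the benefit prediction as a difference in treatment effect by level of cognition.
- **Engagement.** Analyse engagement on cognition within the intervention arm. Note that engagement is retrospective self-report, so recall may itself depend on cognition.
- **Example index.** Replace processing speed with one of the four areas listed in Section 4.1.4.

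The cost is a few sentences and a few extra models on data already collected. The drawback is low precision: a standard error of about 0.20 SD per SD, and 80% power only for moderation of about 0.56 SD per SD with 100 analysed. The plan should say so, so that a non-significant interaction is not read as evidence that cognition makes no difference.
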